## Abstract

**Background:**

Fractional flow reserve (FFR) is a widely used tool for the identification of ischaemia-generating stenoses and to guide decisions on coronary revascularisation. However, the safety of FFR-based decisions in high-risk subsets, such as patients with Diabetes Mellitus (DM) or vulnerable stenoses presenting thin-cap fibro-atheroma (TCFA), is unknown. This study will examine the impact of optical coherence tomography (OCT) plaque morphological assessment and the identification of TCFA, in combination with FFR to better predict clinical outcomes in DM patients.

**Methods:**

COMBINE (OCT–FFR) is a prospective, multi-centre study investigating the natural history of DM patients with ≥1 angiographically intermediate target lesion in three subgroups of patients; patients with FFR negative lesions without TCFA (group A) and patients with FFR negative lesions with TCFA (group B) as detected by OCT and to compare these two groups with each other, as well as to a third group with FFR-positive, PCI-treated intermediate lesions (group C). The study hypothesis is that DM patients with TCFA (group B) have a worse outcome than those without TCFA (group A) and also when compared to those patients with lesions FFR ≤0.80 who underwent complete revascularisation. The primary endpoint is the incidence of target lesion major adverse cardiac events (MACE); a composite of cardiac death, myocardial infarction or rehospitalisation for unstable/progressive angina in group B *vs.* group A.

**Conclusion:**

COMBINE (OCT–FFR) is the first prospective study to examine whether the addition of OCT plaque morphological evaluation to FFR haemodynamic assessment of intermediate lesions in DM patients will better predict MACE and possibly lead to new revascularisation strategies.

*Trial Registration* Netherlands Trial Register: NTR5376

**Electronic supplementary material:**

The online version of this article (doi:10.1186/s12933-016-0464-8) contains supplementary material, which is available to authorized users.

## Background

Diabetes Mellitus (DM) is associated with more rapidly progressive coronary atherosclerosis and increased mortality compared to non-diabetic patients [1, 2]. Fractional Flow Reserve (FFR) is a pressure-derived intracoronary functional index currently recommended in clinical practice guidelines for stenosis assessment in the absence of objective evidence of myocardial ischaemia [3]. Previous studies have shown that FFR-negative lesions (FFR > 0.80) can be safely treated medically, while FFR-positive lesions (FFR ≤ 0.80) benefit from revascularisation [4, 5]. However, in the majority of the FFR trials performed to date, the percentage of DM patients is low [4–6].

More recently, several studies have suggested that FFR-based revascularisation may not be associated with the same reduction in adverse cardiac events as seen in non-DM patients [7–10], even when the presence of microvascular disease, which might imply ischaemia of non-obstructive origin, is taken into consideration [10]. These findings could be explained by the fact that, in patients with DM, adverse cardiac events after ischaemia-driven revascularisation may be related to the presence of more active atherosclerotic disease, resulting in subsequent acute coronary events or obstructive disease progression, rather than to ischaemic burden at the time of revascularisation [11, 12]. However, this hypothesis of more rapid atherosclerosis progression in high risk plaque, is as yet only postulated.

The PROSPECT study demonstrated an ~12 % 3-year rate of future unanticipated major adverse cardiovascular events (MACE) in non-culprit lesions (NCL) [13]. Furthermore, insulin dependent DM was identified as an independent predictor of NCL MACE, in addition to the presence of thin-cap fibroatheroma (TCFA), minimal lumen area (MLA) ≤4 mm^2^, and a plaque burden ≥70 %. Additionally, the rate of future NCL-related MACE was twice as high among patients with DM hosting at least one thin-cap fibroatheroma TCFA, whereas those DM patients without a TCFA had a more benign prognosis, similar to non-DM patients [14].

Although these NCL’s appeared angiographically mild, significant differences in plaque composition between those patients with versus without DM were noted [15]. Separately, Kato et al. have shown that the incidence of TCFA in patients with DM is higher than in patients without DM [16]. As FFR was not measured in PROSPECT, whether these lesions were truly non-ischaemic is unknown, however given the mild angiographic severity (diameter stenosis; median 36.2 % IQR [31.1, 44.2]) this was unlikely. Nonetheless, it has been shown that these high risk IVUS-detected plaque features have no correlation with FFR functional significance of intermediate coronary lesions, and so whether ischaemia is the only factor in the prediction of future adverse cardiac events is questionable [17].

Several studies using intravascular ultrasound (IVUS), have attempted to address the mismatch between the functional and anatomical significance of intermediate coronary lesions, however these have largely focused on quantitative assessments of MLA, lesion length and plaque burden. From these studies, it has been shown that only a mere moderate correlation between IVUS quantitative measurements and FFR exists [17–19].

Optical Coherence Tomography (OCT) is an intravascular imaging modality that provides a spatial resolution 10 times higher than IVUS [20]. Whilst OCT is superior to IVUS in identifying the haemodynamic significance of coronary stenoses, particularly in vessels <3 mm, its low specificity and only modest diagnostic efficacy precludes its use as a substitute for FFR functional stenosis assessment [21]. However, the true benefit of OCT may centre upon its superior ability to detect high risk vulnerable plaque. With the introduction of OCT, our understanding of plaque morphology and the mechanisms of plaque rupture which result in ACS have been significantly advanced [22, 23]. A thin fibrous cap overlying a lipid-rich necrotic core is believed to be the substrate for most vulnerable plaques, and OCT is the only imaging modality that currently can accurately assess fibrous cap thickness [24]. Multiple intravascular imaging studies have shown the the presence of vulnerable plaque characteristics are more prevalent in DM patients compared to non-DM patients and in particular a greater burden of TCFA lesions [25–28]. Due to these characteristics, OCT is being frequently used to evaluate lesion morphology, however, the predictive value of this modality with regard to future MACE is not well studied.

In the COMBINE (OCT–FFR) study, we propose to investigate the incremental value of OCT plaque morphological evaluation added to FFR haemodynamic assessment of intermediate lesions in DM patients in predicting MACE when following an ischaemia-driven revascularization strategy.

## Study design and objectives

The COMBINE (OCT–FFR) is a prospective multi-centre, international study, involving centres in the Netherlands, Germany, Spain, Italy, Switzerland and Poland. The study was approved by the Institutional Review Board of each participating hospital. The study is registered on the Netherlands Trial Registry under the identifier NTR5376 [29]. 

The primary objective of the COMBINE (OCT–FFR) study is to evaluate whether the presence of certain plaque characteristics considered to carry a high-risk (such as TCFA) in lesions with an intermediate-severe angiographic stenosis but which are non-ischaemic (FFR > 0.80) can predict future adverse cardiac events. For this purpose, we have selected to examine only patients with DM, as these patients constitute the sub-population with the fastest progression of coronary atherosclerosis and where recent evidence suggests that deferred revascularisation based upon FFR assessment may not be as safe as in non-DM patients.

The study design is illustrated in Fig. 1. The study population consists of all DM patients with any clinical presentation who undergo FFR assessment in lesions with an intermediate-severe angiographic stenosis. Inclusion and exclusion criteria are presented in Table 1. Lesions which are determined as the culprit lesion in myocardial infarction will not be included, owing to the lack of evidence for FFR in such clinical scenarios. FFR will be performed according to standard protocol using the PressureWire Aeris™ or Certus™ wires, St. Jude Medical, St. Paul, Minnesota, USA. Adenosine is the preferred hyperaemic agent to be administered via the intravenous route at a recommended dose of 140 μg/kg/min to achieve maximum hyperaemia. Should intracoronary adenosine be administered, a dose of 40 μg for the right coronary artery and 80 μg for the left coronary artery is recommended. Once steady-state maximum hyperaemia is achieved, FFR is calculated as the ratio of mean distal intracoronary pressure measured by the pressure wire, and the mean arterial pressure measured through the coronary guiding catheter. In all patients where FFR is performed, OCT assessment using the frequency domain Dragonfly™ OCT system, St. Jude Medical, St. Paul, Minnesota, USA will also take place. Patients with ≥1 lesion which does not undergo revascularisation based upon a FFR negative (>0.80) assessment will be followed clinically. Depending upon the OCT findings, patients without any TCFA (see Additional file 1: Appendix for definition) lesions will form Group A, whilst patients with ≥1 TCFA carrying lesion will form Group B. Finally, patients hosting only FFR-positive target lesions and no other remaining lesions, which have undergone complete index revascularisation either by PCI or CABG will form Group C.

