## Study endpoints

### Primary endpoint

The per patient incidence of target lesion(s) related composite MACE defined as: Cardiac death, myocardial infarction (MI), clinically-driven target lesion revascularisation (TLR) or hospitalisation due to unstable or progressive angina at 18 months in the FFR-negative No-TCFA patients (Group A) as compared to the FFR-negative TCFA patients (Group B).

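### Failure at a revascularised lesion can count as a primary event in Groups A and B, and the TCFA grouping rule is not limited to deferred lesions

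*Protocol article*

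**What the plan says.** Four statements in the protocol article bear on this.

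- **Entry to A or B** (Study design and objectives): "Patients with ≥1 lesion which does not undergo revascularisation based upon a FFR negative (>0.80) assessment will be followed clinically". One deferred lesion is enough; nothing requires all target lesions to be FFR-negative.
- **Split between A and B** (same section): Group A is "patients without any TCFA" lesions, "whilst patients with ≥1 TCFA carrying lesion will form Group B". Neither phrase says which lesions are meant.
- **Group C** (same section): "patients hosting only FFR-positive target lesions and no other remaining lesions", with complete revascularisation at the index procedure. This shows that the article uses the term target lesion for FFR-positive lesions too.
- **Primary endpoint** (Study endpoints): "The per patient incidence of target lesion(s) related composite MACE" at 18 months, A against B. Its components include clinically driven revascularisation of a target lesion. There is no restriction to deferred lesions.

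Other parts are narrower. The abstract describes Group B as "patients with FFR negative lesions with TCFA (group B) as detected by OCT". The primary objective asks about plaque features in lesions with FFR above 0.80. One major secondary endpoint is restricted to TCFA lesions left without revascularisation, and one additional secondary endpoint is restricted to events in FFR-negative lesions.

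**The concern.** Consider a patient with one deferred FFR-negative lesion and one FFR-positive target lesion that was revascularised. Group C is closed to this patient, and no exclusion in Table 1 applies, so the patient is in A or B. Two things follow.

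1. A later event at the treated lesion counts towards the primary endpoint. It says nothing about how an untreated, non-ischaemic lesion with or without TCFA behaves, which is what the primary objective asks.
2. If the only TCFA was seen in the treated lesion, the literal rule in the design section makes this a Group B patient. Under the abstract and the objective it is not.

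At stake are the two definitions on which the primary comparison rests: who is in each group and which events count. The first problem adds events to both groups that have nothing to do with the exposure. The second would mix into Group B patients whose deferred lesions carry no TCFA. In a non-randomised comparison, neither choice should stay open until data have been seen.

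**Working it through.** **The plan's own figure.** The section on follow-up and study management assumes 5% vs 20% at 18 months, one third of patients with at least one FFR-positive lesion, 7% loss, an A:B split between 50:50 and 30:70 either way, and a type I error of 5%. It states that 500 patients give 80% power. Taking the whole third out of A and B leaves 500 × 0.93 × 2/3 = 310. A two-sided pooled test of two proportions then has power 98.2% (155 vs 155), 96.3% (30% in B) or 96.1% (70% in B). The 80% is not reproduced, but the departure is in the safe direction: 80% power would need 246, 263 or 312 patients in total.

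**Ceiling on mixed patients.** The one-third figure counts everyone with at least one FFR-positive lesion, so it includes mixed patients as well as Group C. Let x be the mixed share of all patients. The mixed share of A and B together is m = x / (2/3 + x).

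- x = 1/6 (half of the third): m = (1/6)/(5/6) = 20%.
- x = 1/3 (Group C empty): m = (1/3)/1 = 33%, the maximum.

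**Treated-lesion events.** Assume that 5% and 20% are the risks from deferred lesions, and that a treated lesion adds an independent 7% risk. The 7% is the ceiling the plan assumes for target lesion MACE in Group C. Then A' = 1 − 0.95(1 − 0.07m), B' = 1 − 0.80(1 − 0.07m), and B' − A' = 0.15(1 − 0.07m).

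| m | A' | B' | Ratio | Difference (points) |
|---|---|---|---|---|
| 0 | 5.0% | 20.0% | 4.0 | 15.0 |
| 10% | 5.7% | 20.6% | 3.6 | 14.9 |
| 20% | 6.3% | 21.1% | 3.3 | 14.8 |
| 33% | 7.2% | 21.9% | 3.0 | 14.7 |

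The part of Group A's rate that comes from treated lesions is (5.67 − 5)/5.67 = 12% at m = 10% and (7.22 − 5)/7.22 = 31% at m = 33%. Power hardly moves: at m = 30%, with A and B held at 310, it is 96% for 50:50 and 92% with 70% in B.

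**Misgrouping.** Let q be the share of Group B whose only TCFA was in a treated lesion, and assume that these patients carry Group A's 5% risk. The Group B rate before any treated-lesion events is 0.20(1 − q) + 0.05q: 18.5% at q = 10% and 17.0% at q = 20%. With m = q = 20%, the rates become 6.3% vs 18.2%, and power falls to 89% (50:50) or 81% (70% in B). Since m is the same in both groups here, q = m means that every mixed patient in B is misgrouped, so this is an extreme case for that m. The document gives no value for q.

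**The case against.** The strongest reply is that the text already points to the narrow reading. The sentence splitting A from B directly follows the one on deferred FFR-negative lesions, so the TCFA lesions may simply be those lesions. The abstract, the objective and the group labels in the primary endpoint agree with that. This stands in part. A reader might infer that treated lesions do determine the group; the article supports only that its literal rule allows it. Nor does it say that every lesion with FFR is imaged. The phrase is "In all patients where FFR is performed, OCT assessment", which concerns patients, and misgrouping needs the treated lesion to have been imaged as well.

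Second, counting all target lesions may be deliberate. The Background describes predicting MACE under an ischaemia-driven revascularisation strategy, and the endpoint is per patient. That is a defensible estimand. It is not the one in the stated primary objective, however, and two secondary endpoints do carry a lesion restriction that the primary lacks.

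Third, the effect looks large only as a ratio. The Statistical analysis section reports differences in percentages and in Kaplan–Meier estimates, and the difference barely changes. This stands.

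Fourth, the flow-chart and the additional file with the TCFA definition are not shown, and the full protocol may be clearer. That is possible, but the primary endpoint as printed still has no lesion restriction.

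**Conclusion.** The point holds as a mismatch between definitions and objective. Mixed patients enter A or B, and the primary endpoint as written counts failure at their treated lesions. The TCFA rule is inconsistent between the design section on one side and the abstract and objective on the other; treated lesions can set the group under the literal wording, but it is not established that they will.

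On the plan's rates, a mixed share of 10% to 33% lowers the A/B ratio from 4.0 to between 3.6 and 3.0, and the difference from 15.0 to between 14.9 and 14.7 points. A reader might infer that this threatens the power of the primary comparison. Treated-lesion events alone do not, and a mixed share above about 33% would contradict the plan's one-third assumption. Misgrouping could cost more, but its size is unknown.

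These figures assume that 5% and 20% are deferred-lesion risks, that a treated lesion adds an independent 7%, and that mixed patients are equally common in A and B. If the planned 5% and 20% already include treated-lesion events, the rates would not shift, but the mismatch with the objective would remain.

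**What to change.** - In Study design and objectives, state that Groups A and B are defined by TCFA in the deferred FFR-negative target lesion(s), in line with the abstract.
- In the primary endpoint, state that only events related to those lesions count.
- Report events at target lesions revascularised at the index procedure separately.
- Add a sensitivity analysis of the primary comparison that excludes patients with an index-revascularised target lesion.

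The cost is wording and slightly fewer countable events, which the 96% to 98% power recomputed from the plan's inputs can absorb. The committee that adjudicates endpoints would need to assign each event to a deferred or a treated lesion. The existing target-lesion endpoint already requires events to be related to lesions, but the article does not say that this distinction is recorded.

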**Fig. 1 Fig1:**
[figure not shown]
Study flow-chart

**Table 1 Tab1:** COMBINE OCT–FFR inclusion and exclusion criteria

Inclusion criteria
Age ≥18 years
History of DM with any indication for angiography (Stable Angina Pectoris or any type of ACS)
At least ≥ 1 de novo target lesion in a native coronary segment with a visually estimated diameter stenosis of between ≥40 and ≤80 %
Exclusion criteria
TIMI flow <3 in the target lesion(s)
Target lesion reference diameter <2.0 mm
Left Ventricular ejection fraction <30 %
Malignancy
Life expectancy <2 years
Unwilling or unable to provide informed consent

*DM* denotes diabetes mellitus; *ACS* denotes acute coronary syndrome; *TIMI* denotes thrombolysis in myocardial infarction

## Study endpoints

### Primary endpoint

The per patient incidence of target lesion(s) related composite MACE defined as: Cardiac death, myocardial infarction (MI), clinically-driven target lesion revascularisation (TLR) or hospitalisation due to unstable or progressive angina at 18 months in the FFR-negative No-TCFA patients (Group A) as compared to the FFR-negative TCFA patients (Group B).

### Major secondary endpoints

The per patient incidence of the target lesion(s) related composite MACE: Cardiac Death, MI, clinically-driven TLR or hospitalisation due to unstable or progressive angina between FFR-negative TCFA-positive patients (Group B) and the group of patients with PCI-treated FFR-positive lesions (Group C).The per patient incidence composite MACE: Cardiac death, MI, any clinically-driven revascularisation or hospitalisation due to unstable or progressive angina between FFR- negative TCFA (Group B) and the group of patients with PCI-treated FFR-positive lesions (Group C).The incidence of MACE (Cardiac Death, MI, clinically-driven revascularisation or hospitalisation due to unstable or progressive angina) in patients carrying any non-revascularised TCFA lesion (target or elsewhere within the assessed coronary segments) compared to patients without any identified TCFA lesions.

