## Follow-up data collection and study management

Patient demographics and clinical data at inclusion are collected online in an electronic database (CRO Diagram, Zwolle, The Netherlands). The first 2 patients included in all centres will be fully monitored to identify inconsistent data. Upon discharge and after the intended follow-up period of 18 months, data will be collected at visits at outpatient clinics or, if not feasible, by telephone follow-up and/or a medical questionnaire, carried out by staff who are blinded. Follow-up beyond 18 months is intended, should funding permit. During visits and telephone calls, patients will be interviewed regarding repeat hospitalisations, revascularisation procedures, and myocardial infarction (MI) during follow-up. In case of death, information will be obtained from the patient’s medical chart, local institution and by contact where required with the patient’s cardiologist/general practitioner. FFR and OCT core laboratory will be based at an external independent research centre, in addition to overall trial coordination, data management and study monitoring (CRO Diagram, Zwolle, the Netherlands). An independent clinical events committee will adjudicate all potential clinical endpoints.

Whilst an observational study, without randomisation, in order to confer meaning to the results derived, a power calculation has been made to estimate a projected number of patients that would allow observation of meaningful differences in MACE rates between the above mentioned subgroups of patients. The primary endpoint event rate at 18 months in the A and B group respectively are assumed to be 5 and 20 % respectively. Furthermore, we assume that 1/3 of the patients will have at least one lesion with a positive FFR (≤0.80) as shown from the major FFR trials [4, 5].

An equal distribution of patients between subgroups A and B is expected (50 % in each group) however the power calculation takes in account variations up to 20 % (i.e. an unequal TCFA distribution in both directions up to 30 vs. 70 %). 

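### On the patient-level Group B versus Group C endpoint, untreated residual disease is tied to TCFA by group definition, so an excess in Group B cannot by itself be attributed to TCFA

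*Protocol article*

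**What the plan says.** All places are in the protocol article.

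- **Group C** (Study design and objectives): "patients hosting only FFR-positive target lesions and no other remaining lesions, which have undergone complete index revascularisation either by PCI or CABG". The Additional secondary endpoints repeat the condition that Group C has nothing left untreated.
- **Groups A and B** (same section): "Patients with ≥1 lesion which does not undergo revascularisation based upon a FFR negative (>0.80) assessment will be followed clinically". Of these, "patients with ≥1 TCFA carrying lesion will form Group B", and patients without TCFA form Group A. The number, TCFA status and treatment of a Group B patient's other lesions are not restricted.
- **Endpoints** (Major secondary endpoints): the first B-versus-C endpoint counts target-lesion events. The second is per patient and counts "any clinically-driven revascularisation or hospitalisation due to unstable or progressive angina between FFR- negative TCFA (Group B" and Group C, together with cardiac death and MI.
- **Hypothesis** (Abstract, Methods): TCFA patients are expected to do worse than patients without TCFA, "also when compared to those patients with lesions FFR ≤0.80 who underwent complete revascularisation".
- **A versus C** (Additional secondary endpoints): listed for target-lesion MACE only.
- **Planning rates** (Follow-up data collection and study management): 18-month primary-endpoint rates in A and B are "assumed to be 5 and 20 % respectively". Target-lesion MACE in C is taken not to exceed 7%.

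**The concern.** The two groups differ in how much untreated disease they are allowed to keep, and the endpoint is wide enough to register that difference. Suppose a Group B patient has one deferred TCFA lesion and other untreated disease. A revascularisation of that other disease counts as an event in B. A patient left with untreated disease cannot enter Group C at all. A patient with one treated FFR-positive lesion and one deferred lesion is also shut out of C and falls into A or B.

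The hypothesis links the worse outcome in B to TCFA. On this endpoint B could do worse because it has more disease left to cause events, even if TCFA added no risk. A positive result could then be read as support for treating TCFA lesions when it reflects, at least in part, the way the groups were formed.

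**Working it through.** **1. The plan's own figures.** 500 enrolled with 7% loss leaves 500 × 0.93 = 465. Taking the stated one third with a positive FFR as the Group C share (an assumption, since that third is defined by at least one positive lesion) gives 155 in C and 310 in A and B, or 155 each at an equal split. With a two-sided 5% test of two proportions, power is 98.2% for A versus B (5% v 20%) and 92.2% for B versus C (20% v 7%). Both exceed the stated 80%. That is a separate matter and does not bear on this point. No rate is given for the patient-level composite in any group.

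**2. The definitions side by side.**

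| | Group A | Group B | Group C |
|---|---|---|---|
| Untreated FFR-negative lesion | at least one | at least one | none |
| TCFA in the lesions assessed | no | yes | not used to define the group |
| Limit on other untreated lesions | none stated | none stated | none may remain |

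Between B and C, having an untreated lesion coincides exactly with group membership. Between A and B it does not.

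**3. Can adjustment separate them?** Statistical analysis plans a multivariate regression. For B versus C, an indicator of any untreated lesion is always 1 in B and always 0 in C. With no overlap, its effect cannot be estimated apart from the group effect. For A versus B the number of untreated lesions can vary in both groups, so adjustment is possible there.

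**4. What would separate them.** On the risk-difference scale, B − C = (B − A) + (A − C). The first term compares two deferred groups that differ by TCFA. The second compares deferred patients without TCFA with completely revascularised patients, so it carries residual disease, ischaemia at baseline and treatment effects, but not TCFA. With the plan's target-lesion rates: 20 − 7 = (20 − 5) + (5 − 7), that is 13 = 15 + (−2) points. The planned gap thus comes entirely from B − A. For the patient-level composite the document lists neither A versus C nor A versus B, so neither term can be read off.

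**5. Can a size be derived?** The only figure bearing on residual-lesion risk is the roughly 12% three-year MACE rate in non-culprit lesions (Background), about 6% at 18 months if linear. Let s be the share of B with residual non-target disease (not in the document; assumed 0.3 to 0.6). With no TCFA effect, start B at the document's 5% for FFR-negative patients without TCFA:

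- s = 0.3: 0.05 + 0.95 × 0.3 × 0.06 = 6.7%
- s = 0.6: 0.05 + 0.95 × 0.6 × 0.06 = 8.4%

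Against 7% in C the risk ratio is 0.96 to 1.20. It crosses 1 at s = 0.02 / (0.95 × 0.06) = 0.35. The 7% is itself a target-lesion rate, and C's patient-level rate would be at least as high. The sign therefore rests on inputs that the document does not give.

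**The case against.** The strongest case on the other side has four parts.

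- **The contrast is declared.** The hypothesis names as comparator "those patients with lesions FFR ≤0.80 who underwent complete revascularisation". B and C also differ in FFR and in treatment, so the comparison was never going to isolate TCFA. This stands. It means that the comparison should stay; it does not license attributing its result to TCFA.
- **TCFA is tested elsewhere.** A versus B is the primary comparison, and the third major secondary endpoint compares MACE in patients with a non-revascularised TCFA lesion against patients without any. This largely stands and is the main reason the point is minor. But the primary counts target-lesion events only, and the no-TCFA side of the third endpoint is not stated to be limited to Group A.
- **The asymmetry may be narrower than it looks.** Under an ischaemia-driven strategy, FFR-positive lesions would be treated, so the lesions left in B may mostly be the deferred target lesions. The condition on Group C may also concern intermediate lesions only, with milder plaque allowed in both groups. The text does not settle this. Either reading shrinks the asymmetry, but B still keeps at least one untreated lesion by definition.
- **Covariates belong in the analysis plan.** True in general, and their absence from an article is no fault. Here, though, the lack of overlap comes from the group definitions, so no choice of covariates fully removes it.

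**Conclusion.** The point holds as a limit on interpretation. On the patient-level B-versus-C endpoint, residual untreated disease is confounded with TCFA by group definition, and an excess in B cannot by itself be attributed to TCFA. This rests on reading the Group C condition as it is written.

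A reader might go further and infer that the comparison is tilted against B by a known amount. Starting B at 7%, the rate assumed for C, gives 0.07 + 0.93 × 0.3 × 0.06 = 8.7% to 0.07 + 0.93 × 0.6 × 0.06 = 10.3% against 7%, a risk ratio of about 1.2 to 1.5. The document does not support that:

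- It sets a patient-level rate in B against a target-lesion rate in C.
- It passes over the document's own 5% for FFR-negative patients without TCFA.
- It applies to B alone a rate from lesions with a median stenosis of 36.2%. At least half of them lie below this study's 40% entry threshold, and Group C may carry such plaque too.
- That rate includes TCFA lesions, so it does not fit a scenario in which TCFA has no effect.

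Nor is the net direction certain: residual disease pushes events towards B, while C is selected for ischaemic disease and has its own stent- or graft-related events.

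Severity is minor. One secondary endpoint is concerned, and the primary A-versus-B comparison is unaffected because both groups keep at least one untreated lesion.

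**What to change.** Keep B versus C as declared. Add patient-level A versus C and A versus B on the same composite at 18 months. State in advance that a B-versus-C difference will be attributed to TCFA only if A versus B supports it and A versus C shows no similar difference. The data are already collected, so the cost is analysis work and a few sentences of text.

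Restricting Group B to patients with no untreated lesion other than the deferred target lesion(s) may be reported as a sensitivity analysis, with residual lesions taken from the index angiogram. It does not replace the A-versus-C comparison, because a restricted B still keeps its deferred lesion. Its downside is a smaller Group B. As a guide, with the plan's target-lesion rates (20% v 7%) and 155 in C:

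| Share of B retained | Patients in B | Power |
|---|---|---|
| 1.0 | 155 | 92.2% |
| 0.7 | 108.5 | 87.1% |
| 0.5 | 77.5 | 80.9% |
| 0.4 | 62 | 76.1% |
| 0.3 | 46.5 | 69.5% |

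The share that would qualify is not in the document. Power stays near 80% only if about half of Group B or more is retained, which is why the restriction suits a sensitivity analysis better than the main comparison.
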